**Methods:**

The PERYTON-study is a prospective multicentre open phase III randomised controlled trial. We aim to include 538 participants (269 participants per treatment arm) with a BCR after prostatectomy, a PSA-value of < 1.0 ng/mL and a recent negative PSMA PET/CT scan. Participants will be randomised in a 1:1 ratio between the conventional fractionated treatment arm (35 × 2 Gy) and the experimental hypofractionated treatment arm (20 × 3 Gy). The primary endpoint is the 5-year progression-free survival after treatment. The secondary endpoints include toxicity, quality of life and disease specific survival.

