### Primary endpoint

The primary endpoint is 5-year progression-free survival (PFS), defined as biochemical progression, clinical progression, loco-regional progression, distant progression or the start with hormonal therapy, whichever occurs first. Biochemical progression will be defined as a PSA value of 0.2 ng/mL higher than the PSA Nadir (defined as the lowest PSA value ≥3 months after completion of treatment). Participants with no change or an increase in PSA level after sEBRT will be defined as non-responders.

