### Secondary endpoints

Acute grade ≥ 2 gastrointestinal (GI) and genitourinary (GU) toxicities measured 3 months after treatment using both physician-reported score (Common Terminology Criteria for Adverse Events (CTCAE), version 5.0) and patient-reported questionnaires (RTOG Acute Radiation Morbidity Criteria using adapted RTOG/EORTC acute Radiation Morbidity questionnaires);3- and 5-year late grade ≥ 2 GI and GU toxicities, measured using both physician-reported score (CTCAE version 5.0 criteria) and patient-reported questionnaires (RTOG/EORTC criteria);QoL, using the European Organization for Research and Treatment of Cancer (EORTC) QoL thirty item score questionnaires (QLQ-C30) for health-related QoL and the EORTC QoL prostate carcinoma module (QLQ-PR25) is used;Metastasis-free survival: Randomisation date to the date of metastases reported by imaging;PCa-specific mortality;Overall survival at 5 years from date of randomisation.

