### Sample size considerations

A systematic review and meta-analysis reported that each additional Gy in the conventional sEBRT-arm is possibly associated with a 2% higher bPFS, independent of other factors. These results imply that our biological dose escalated effect with hypofractionation will result in 16% higher bPFS (8 Gy × 2% per Gy). However, this meta-analysis did not include series using a radiotherapy dose above 70 Gy. In higher dose series as proposed in this study, the relative benefit may be lower and consequently an expected benefit of 16% may be too optimistic. Therefore, a conservative 12% higher 5-year bPFS in the experimental arm of 20 fractions of 3 Gy compared to the conventional sEBRT schedule of 35 fractions of 2 Gy (70 Gy) has been chosen. This estimated benefit of 12% is also supported by a meta-analysis including conventional and hypofractionated regimens addressing the influence of fraction size and the total dose effect on bPFS and toxicity [28].

The results of the GETUG-AFU 16 trial showed a 5-year bPFS of 62% with the conventional fractionated radiotherapy protocol [26]. We used this percentage (62%) for the 5-year bPFS in our conventional sEBRT treatment arm. Following the above mentioned literature, we hypothesize that with the experimental regimen the bPFS can be improved from 62 to 74%. Using an alpha of 5% and a study power of 81%, the required sample size is 235 participants per treatment arm. Assuming a dropout of 12%, we need to recruit 269 participants per treatment arm: 538 in total.

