### Interim analysis

Dose-limiting constraints for rectum and bladder will be used (Table 2) and a QA process is mandatory before the start of inclusion in the participating centres. Toxicity is expected to be equivalent in both arms. Nevertheless, a slight increase in acute toxicity in the experimental arm might be expected due to the short overall treatment time [29]. Therefore, we will perform an interim analysis after the inclusion of 25% of the estimated number of participants (135 participants) to identify any early signs of excessive (unexpected) acute toxicity. Grade 3 CTCAE acute toxicity will be used for this interim analysis; i.e., > 5% difference in grade 3 toxicity between the experimental and control arm. If this acute toxicity difference exceeds 5%, a formal interim analysis will be performed with a nominal *p* value < 0.001 according to the Haybittle-Peto alpha spending function, to indicate statistical significance [30]. The interim analysis will be performed by an independent statistician, and the results will be shared with the principal investigators who will judge after informing the ethical committee whether continuation of the study is safe.

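### The interim toxicity comparison goes to the principal investigators, who also judge continuation, and the text does not clearly limit this to a crossed 5% threshold

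*Protocol article*

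**What the plan says.** The Interim analysis section of the protocol article sets out the whole route.

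- **Timing.** The look comes after 25% of the planned number, given as 135 participants. Sample size considerations gives the total: "we need to recruit 269 participants per treatment arm: 538 in total".
- **Quantity.** The screen is a difference of more than 5% in grade 3 CTCAE acute toxicity between the experimental and control arms. If it is exceeded, a formal test at a nominal p below 0.001 follows.
- **Analyst.** An independent statistician does the work.
- **Recipient and decision-maker.** "the results will be shared with the principal investigators who will judge after informing the ethical committee whether continuation of the study is safe".

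Three other statements bear on the consequences. The abstract describes a "prospective multicentre open phase III randomised controlled trial". Secondary endpoints has late toxicity "measured using both physician-reported score (CTCAE version 5.0 criteria) and patient-reported questionnaires", and acute toxicity at 3 months is measured in the same two ways. The primary endpoint counts several forms of progression "or the start with hormonal therapy, whichever occurs first".

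**The concern.** An independent analyst protects a trial when those who run it do not see the emerging comparison unless they need to act on it. Here the quantity analysed is itself a difference between arms, so sharing the results means sharing the comparison. The principal investigators then also decide, and the committee that is told beforehand has no stated say.

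In an open trial, someone who has seen an early toxicity difference can grade later men differently, or offer the trial more or less readily to some men. The Interim analysis section already expects a slight acute increase in the experimental arm, so an observed excess could reinforce that expectation. Most exposed are the physician-reported toxicity comparison and the mix of men recruited afterwards. A decision to continue after a signal is also less convincing when only those running the trial have judged it.

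**Working it through.** **1. The plan's own figure.** 25% × 538 = 134.5, rounded up to 135. This reproduces the stated number.

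**2. Men still to be enrolled.** There are two cases, because the article does not say whether the look uses the grades available at the 135th inclusion or waits for that man's assessment.

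- At the trigger: 538 − 135 = 403, and 403/538 = 74.9%.
- After waiting: treatment takes 4 or 7 weeks (Table 3) and acute toxicity is measured 3 months after treatment (Secondary endpoints), a lag of about 4.5 months. No pause in accrual is stated, and no accrual rate is given, so I assume 10 to 20 men per month.
  - At 10 per month: 403 − 45 = 358, or 67%.
  - At 20 per month: 403 − 90 = 313, or 58%.

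So 75% is an upper limit, and 58–67% is the range under the assumed accrual.

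**3. Late toxicity.** At the same assumed rates, 135 inclusions take 135/20 = 6.75 to 135/10 = 13.5 months. Adding 4.5 months, results are known about 11 to 18 months after the first inclusion. No man has then reached his 3-year assessment, so all 3-year and 5-year grading lies ahead, although some earlier follow-up grades will already exist.

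**4. How much is left to judgement.** Inputs are about 67 men per arm, a pooled z-test and two-sided p < 0.001 (critical value 3.29). The article gives no control rate for grade 3 toxicity, so 2%, 5% and 10% are assumed. The smallest difference d that reaches significance solves d / √[p̄(1 − p̄) × 2/67] > 3.29, where p̄ = control rate + d/2. The 5% screen is read as percentage points. The chance columns are exact binomial probabilities with equal true rates.

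| Assumed control rate | Difference needed for p < 0.001 | Chance of an experimental excess above 5 points | Chance of a difference above 5 points in either direction |
|---|---|---|---|
| 2% | about 18 points | 2% | 3% |
| 5% | about 21 points | 8% | 16% |
| 10% | about 24 points | 16% | 31% |

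Worked example at 5%: d = 0.205 gives p̄ = 0.1525, standard error 0.0621 and z = 3.30.

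Between 5 and roughly 18–24 points, the screen is crossed but the formal test cannot be significant. In that wide zone the outcome depends on the judgement of whoever holds the results.

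**5. Is sharing conditional?** The conditional sentence calls the test that follows a crossed screen a formal interim analysis. The next sentence speaks only of the interim analysis and its results. That may mean the formal, conditional step or the whole procedure, and the text does not settle which. On the wider reading, results by arm are always passed on. On the narrower one, with no true difference, they are passed on only with the probabilities in the last two columns, depending on whether the screen is one-directional.

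**The case against.** The case against has real force, and several stronger readings should be set aside.

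- **A reader might infer that the physicians who enrol, treat and grade the remaining men will know the result.** The article names only the principal investigators. It does not say that they grade CTCAE or that site physicians receive anything, and the trial is multicentre. That principal investigators may include treating or grading physicians is a reasonable inference, not a stated fact.
- **A reader might infer that results are shared whatever they show.** This is one of two readings. The defect is that the text does not choose between them.
- **A reader might infer that 75% of men enrol after the results are known.** That holds only at the trigger; the assessment lag lowers it.
- **A reader might infer bias in the primary endpoint through the start of hormonal therapy.** The look covers grade 3 acute toxicity and no progression data. Biochemical progression follows a fixed PSA rule on scheduled tests. The article shows no direct route from an acute toxicity comparison to the timing of hormonal therapy, so any effect is indirect.
- **A reader might infer that no independent oversight exists.** The article condenses a fuller protocol, so an unnamed committee is not a finding. The finding is the routing that the article itself states.

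Two further objections stand in part. Physicians in an open trial already know allocation and already expect a slight acute excess, so the bias added by seeing the result cannot be separated from what open grading carries anyway. Patient-reported toxicity is collected in parallel and gives some check, though patients too know their arm.

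None of this alters the stated rule: the results go to the principal investigators, who judge continuation, with the ethics committee informed only.

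**Conclusion.** The point holds in a limited form. The stated route gives a between-arm toxicity comparison to the people who run the trial and leaves the continuation judgement to them. It does not clearly restrict disclosure to the case in which a decision is needed. That weakens the protection that an independent statistician was meant to give.

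The exposure is up to 75% of men still to be enrolled (58–67% under the assumed accrual and lag), plus most late toxicity grading. The outcomes at risk are the physician-reported toxicity comparison and recruitment. The size of any bias cannot be derived from the document, and I put no figure on it. The conclusion also assumes that at least some principal investigators treat or grade participants, or speak with those who do. It is worth correcting because the correction costs little, not because harm has been shown.

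**What to change.** Amend the Interim analysis section to state that:

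1. when the difference in grade 3 acute toxicity is 5% or less, the independent statistician reports only *threshold not crossed*, with no rates by arm;
2. arm-level results are released only when the threshold is exceeded, and then only to those who must make the continuation decision;
3. the ethics committee's view is obtained before they decide, where the committee accepts that role;
4. arm-level results are not passed on to physicians who grade toxicity.

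Item 3 is the most open to debate, since the article does not show that the committee has that role or the capacity for it. The other items do not depend on it. If the look has already been taken, record who received arm-level results and when, so that the trial report can say so.

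The cost is wording; sample size, alpha and power do not change. The principal investigators see less detail when there is no signal, and a decision after a crossed threshold may take slightly longer. The short message still reveals that the difference was at most 5%, which is far less than rates by arm.

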## Discussion

Salvage external beam radiation therapy (sEBRT) is an established treatment option for BCR after RP, with a 5-year bPFS up to 60%. Which means that 40% of the patients receiving sEBRT experience a second BCR after radiotherapy. This suggests that sEBRT does not benefit those patients with a second BCR, while exposing them to treatment-related side effects. Hence, there is a need to improve the treatment outcome of sEBRT.

Predisposing factors for BCR after sEBRT may either originate at the primary tumour site, indicating insufficient local treatment, or from disease outside the prostate bed (i.e., occult metastases), suggesting metastatic disease for which local sEBRT is not appropriate.

The PERYTON-study aims to increase the effectiveness of sEBRT after radical prostatectomy by:Excluding patients with metastatic disease for sEBRT with the (early) use of the PSMA-PET/CT scan as screening imaging modality before the inclusion of patients.Using an hypofractionated radiotherapy schedule of 20 × 3 Gy in sEBRT to escalate the biological effective radiation dose to the prostate bed.

In conclusion, the PERYTON-trial is, to our knowledge, the first prospective phase III RCT, using the PSMA PET/CT-scan as standard imaging modality and investigating the potential benefit of a hypofractionated sEBRT schedule of 20 × 3 Gy = 60 Gy compared to the conventional fractionated standard of 35 × 2 Gy = 70 Gy.

## Data Availability

Not applicable.

## Abbreviations

PCa: Prostate cancer
RP: Radical prostatectomy
BCR: Biochemical recurrence
sEBRT: Salvage external beam radiotherapy
PSMA PET/CT: Prostate-specific membrane antigen positron emission tomography/computed tomography
bPFS: Biochemical progression-free survival
EQ D2: Equivalent Dose at 2 Gy
QoL: Quality of life
RCT: Randomised controlled trial
PFS: Progression-free survival
PSA: Prostate specific antigen
GI: Gastrointestinal
GU: Genitourinary
QA: Quality assurance
GTV: Gross tumour volume
CT-scan: Computed tomography scan
CTV: Clinical target volume
PTV: Planning target volume
IMRT: Intensity modulated radiation therapy
VMAT: Volumetric modulated arc therapy
OAR: Organ at risk
ADT: Androgen deprivation therapy
